#### Phase 2: maintenance phase (6–12 months)

During Phase 2 (6–12 months), a mobile health application will be implemented to support weight maintenance and sustained adherence. The application will enable dietitians to update clinical data and monitor participants’ dietary intake, physical activity, and adherence patterns. Participants will receive tailored meal examples, weekly reminders promoting dietary compliance, physical activity, and stress management, and will log in their 24-h intake and exercise sessions. A secure chat feature will facilitate ongoing communication and individualized feedback, allowing early identification and management of potential adherence barriers.

#### Intervention fidelity

A standardized counseling manual will be used by all dietitians, including structured questionnaires and checklists to ensure consistency in intervention delivery. Dietitians will undergo dedicated training sessions to standardize and harmonize the protocol implementation. Participants will receive individualized counseling sessions and will report dietary adherence using repeated 24-h dietary recalls and food records.

Detailed descriptions of dietary prescriptions, counseling content, and behavioral strategies are provided in the IM Step 4 section.

### Study procedures

Upon enrollment, participants will undergo baseline assessment, including anthropometric measurements, biochemical testing, and completion of standardized questionnaires. Each participant will have an individual study file containing anthropometric, biochemical, and body composition data. Standardized questionnaires will be used to collect demographic and lifestyle information and to assess diabetes-related knowledge, dietary and medication adherence, stress, sleep quality, and PA levels. Participants will attend monthly follow-up visits with dietitians, and laboratory assessments will be performed every three months throughout the trial.

### Outcomes

The primary outcome is diabetes remission at 6 months (HbA_1c_ < 6.5% with or without diabetes medication).

Secondary outcomes include sustained remission at 12 months, changes in body weight and body composition, glycemic control (fasting glucose, HbA1c, fasting insulin), lipid profile, sleep quality, PA, psychological stress, and inflammatory markers. Secondary outcomes will be assessed at baseline and every 3 months and analyzed exploratorily.

### Statistical methods

All analyses will be conducted according to the intention-to-treat principle. Baseline demographic and clinical characteristics will be summarized descriptively by randomized group using means ± standard deviations or medians (interquartile ranges) for continuous variables and frequencies and percentages for categorical variables. In accordance with SPIRIT recommendations, no formal statistical testing will be performed for baseline comparisons.

The primary outcome, diabetes remission—defined as HbA1c < 6.5% irrespective of glucose-lowering medication use—will be analyzed using logistic regression models or generalized mixed-effects logistic models when assessed longitudinally, with intervention group as the primary predictor. Remission prevalence will be reported overall and stratified by medication status (remission achieved without medication and remission achieved while continuing pharmacotherapy). Effect estimates will be presented as odds ratios with 95% confidence intervals.

Secondary outcomes will include changes in metabolic parameters (body weight, BMI, lipid profile, glycemic profile, inflammatory markers, and indices of insulin sensitivity) as well as behavioral and physiological outcomes (PA, sleep quality, and stress). Continuous outcomes will be analyzed using linear mixed-effects models with fixed effects for intervention group, time, and group-by-time interaction, and a random effect for participants to account for repeated measurements. The group-by-time interaction term will be used to assess differential effects between the two dietary interventions.

The effectiveness of the educational component will be evaluated by examining the association between education exposure or knowledge change and the primary and secondary outcomes using multivariable regression models adjusted for relevant baseline covariates.

Missing data will be handled using appropriate statistical methods where applicable. Statistical significance will be set at *p* < 0.05. All analyses will be performed by a blinded statistician using standard statistical software.

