### Sample size calculation

Sample size estimation was based on the primary outcome of diabetes remission at 6 months, defined as HbA1c < 6.5% with or without discontinuation of glucose-lowering medication, a definition used in a large meta-analysis (27). The same meta-analysis reported that LC diets (<130 g/day) were associated with a remission rate of approximately 57% at 6 months.

For the MD group, a remission rate of approximately 15% at 12 months was reported in medication-naïve individuals (49). Given that remission rates are known to be lower among individuals receiving glucose-lowering therapy, as demonstrated in large observational cohorts (50, 51), this supports a conservative estimate for the present study population, which includes participants treated initially with oral antidiabetic medications. Furthermore, as no large randomized trials have reported diabetes remission at 6 months following an MD, and considering evidence from long-term intervention studies showing a decline in remission rates over time, including the DiRECT (52) and Look AHEAD (53) trials, a conservative remission rate of 15% at 6 months was assumed for the MD in the present trial.

It should be acknowledged that the remission estimates used for the sample size calculation were derived from studies conducted in different medication contexts. In both cases, remission was based on the same glycemic threshold (HbA1c < 6.5%). However, the estimate for the MD was derived from a study conducted in medication-naïve individuals, whereas the remission estimate for the LC diet was obtained from studies in which participants were receiving glucose-lowering therapy and remission was defined irrespective of medication use. Therefore, the two estimates are not fully comparable. Nevertheless, in the present trial, remission is defined consistently for both intervention arms as HbA1c < 6.5% regardless of medication use. In the absence of randomized trials reporting remission following an MD in medicated populations, the 15% rate was retained as a conservative estimate for the power calculation.

Using these expected remission rates (57% vs. 15%) and a two-sided *α* level of 0.05 with 80% power, the required sample size was estimated at 38 participants. To account for an anticipated attrition rate of approximately 20%, a total sample size of 50 participants was targeted.

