### Randomization

Randomization (by minimization) was performed in the two arms using the computer-generated program “QMinim,” which ensures balance across pre-specified covariates, including age, sex, diabetes duration, and baseline BMI. The allocation sequence was generated by a research assistant who is not involved in enrolling participants or delivering the interventions.

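### The primary logistic model names no covariate; adding continuous baseline HbA1c, already measured in everyone, would be a nearly free improvement

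*Protocol article*

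**What the plan says.** The endpoint is binary and fixed in time: "The primary outcome is diabetes remission at 6 months", met by an HbA1c below 6.5% whether or not medication continues (Outcomes).

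The Statistical methods section analyses it by logistic regression, or by a mixed-effects logistic model if assessed longitudinally, "with intervention group as the primary predictor". The effect measure is an odds ratio with a 95% interval. No covariate is named for this model. Adjustment for baseline covariates is mentioned in that section only for the analysis of the educational component.

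The Randomization section describes minimisation, "which ensures balance across pre-specified covariates, including age, sex, diabetes duration, and baseline BMI". Baseline HbA1c is not named there. It is available for everyone, because Study procedures and Outcomes provide for baseline biochemical testing and list HbA1c among the measures taken at baseline and every three months.

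**The concern.** The article puts effort into balancing four baseline factors but does not carry them into the description of the primary analysis. It also does not name the baseline variable that should matter most. The endpoint is a cut on HbA1c, so where a participant starts is likely to matter greatly for which side of 6.5% they end on. The Eligibility section, as printed, gives no lower HbA1c limit and admits people on oral drugs. Under that text a participant could already be below the threshold at enrolment, and the endpoint counts them regardless of medication.

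Two things are at stake in a trial with about 20 evaluable participants per arm. One is precision that could be had without new data. The other is conditional bias if the arms happen to differ in baseline HbA1c. There is also a question of definition. Odds ratios are non-collapsible, so adjusted and unadjusted odds ratios differ even under perfect balance, and the text as it stands does not settle which one is primary.

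**Working it through.** **Inputs.** From Sample size calculation: the LC diets "were associated with a remission rate of approximately 57% at 6 months"; for the MD, "a conservative remission rate of 15% at 6 months was assumed for the MD in the present trial"; two-sided "level of 0.05 with 80% power"; "the required sample size was estimated at 38 participants"; 50 targeted after about 20% attrition. Assumed, because not stated: 1:1 allocation; baseline HbA1c effect 0 to 2.0 log-odds per SD; each minimisation factor 0 to 0.5 log-odds (per SD, or per unit when coded ±1).

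**1. The plan's own figure.** Arcsine formula, with h = 2·asin√0.57 − 2·asin√0.15 ≈ 0.916:

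n per arm = 2 × (1.960 + 0.842)² / h² = 18.7, so 19 per arm and 38 in total, as stated.

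The pooled two-proportion formula gives 20 per arm, 40 in total, and 40/0.8 = 50. Its power is 79.4% at 19 per arm, 81.5% at 20 and 89.6% at 25. The stated size therefore rests on an unadjusted comparison.

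**2. Expected events.** 20 × (0.57 + 0.15) = 14.4 at 20 per arm; 25 × 0.72 = 18 at 25 per arm. Arm plus HbA1c has two slopes, or 7 to 9 events per slope. Arm plus HbA1c plus four factors has six slopes: 14.4/6 = 2.4 to 18/6 = 3 events per slope.

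**3. Chance imbalance.** Where HbA1c is not balanced by design, the between-arm difference in its mean has an SD of √(2/25) = 0.28 baseline SDs at 25 per arm.

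**4. Power at 20 per arm, 57% vs 15%.** Firth logistic regression, penalised likelihood-ratio test, simple 1:1 allocation, 1,000 runs per scenario (Monte Carlo SE about 1 point). Ranges cover minimisation-factor effects of 0 and 0.4 log-odds per SD.

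| HbA1c, log-odds per SD | Unadjusted | + HbA1c | + HbA1c and four factors |
|---|---|---|---|
| 0 | 80–82% | 80–81% | 76–82% |
| 0.5 | 81–82% | 83% | 78–81% |
| 1.0 | 78–80% | 85–86% | 81–83% |
| 1.5 | 80% | 89–91% | 86–88% |
| 2.0 | 80–81% | 91–94% | 88–89% |

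Type I error of the adjusted tests was 3.9–5.5%.

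A separate Firth simulation, with each factor at 0.3 log-odds per SD, gave unadjusted / + HbA1c / all five of 79/80/79% at 0, 82/87/83% at 1.0 and 78/93/88% at 2.0. Type I error was about 5–6%.

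The gain from HbA1c alone is therefore about 0 to +1 points at 0, +5 to +8 at 1.0, +9 to +11 at 1.5 and +10 to +15 at 2.0.

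**5. With minimisation actually simulated.** Four binary factors, biased coin 0.8, N = 40, Wald test, 1,000 runs per scenario:
- HbA1c alone: +0.3 points (74.6% to 74.9%) with nothing prognostic, rising to +7.8 points (77.8% to 85.6%) at 1.5 log-odds per SD.
- Four factors alone: −0.7 to +1.9 points.
- All five: −6.2 (77.8% to 71.6%) to +1.9 points.
- Type I error of the unadjusted test: 3.0–4.0%; adjusted for the four factors: 4.7–6.0%.

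**6. If all 50 are analysed** (simple allocation, Wald test), HbA1c alone changes power by −1 to +6 points. The gain is smaller because unadjusted power is already near 90%.

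**The case against.** The strongest reply is that the text does not describe an unadjusted model. A reader might infer that the model contains only intervention group, but a primary predictor need not be the only term. This is a condensed article, and an unseen analysis plan may list covariates. That stands: silence is no error, and the point is put as an improvement to what is specified. Similarly, the word introducing the minimisation factors does not close the list, so HbA1c is best described as not named there.

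A reader might also infer that power already paid for is being wasted. The article does not support that. The 38 reproduces without adjustment, so no adjustment gain was budgeted. The gain comes from HbA1c, while the four minimised factors add essentially nothing. Nor are false positives inflated: under simulated minimisation the unadjusted test was slightly conservative.

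The objection that the benefit is assumed is fair. With HbA1c at 0 or 0.5 log-odds per SD, the five-covariate model lost about 2 to 4 points against the unadjusted test in further Firth runs (82% to 78%; 80% to 78%). This counts against loading all five covariates into the primary model. It does not count against HbA1c alone, which cost essentially nothing when it was not prognostic.

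**Conclusion.** The point holds as a recommendation to name baseline HbA1c in the primary model. At 20 per arm the change in power from that one covariate is about 0 to +15 points over an assumed effect of 0 to 2.0 log-odds per SD. At 1.0 it is about +5 to +8; at 1.5 it is about +8 with a Wald test and +9 to +11 with the penalised likelihood-ratio test. Type I error of the penalised test stays near 5%. Adjustment also removes conditional bias from a chance baseline difference.

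Adding the four minimisation factors aligns analysis with allocation but brings no power, and costs up to about 6 points relative to HbA1c alone with about 14 events.

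These sizes assume 1:1 allocation, the planned rates of 57% and 15%, a logit linear in HbA1c and normally distributed HbA1c. The article does not fix the prognostic strength, so the range and not a single figure is the result. The stated sample size is unaffected.

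**What to change.** Before unblinding, specify the primary 6-month analysis as follows:

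- Remission regressed on arm and baseline HbA1c, the latter as a continuous linear term.
- Firth's penalty with a penalised likelihood-ratio test, because events are few.
- A standardised risk difference beside the odds ratio, with a statement that the odds ratio is conditional on baseline HbA1c.
- Two sensitivity analyses: the unadjusted model, and the primary model plus age, sex, diabetes duration and BMI.

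If an existing analysis plan already fixes the covariates, check it against this list and state the choice in the protocol.

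The cost is wording only, since every covariate is already collected. The small downsides are a penalised instead of an ordinary logistic fit, and a sensitivity model with the four factors that may be a few points less powerful than the primary one.

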### Intervention

Participants are randomly allocated to one of two dietary intervention arms: a low-calorie MD or a low-calorie LC diet. The intervention is delivered in two sequential phases: an initial weight-loss induction phase followed by a maintenance phase.

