#### Phase 1: weight-loss induction (0–6 months)

During Phase 1, participants are randomly divided into two groups. One group follows an LC diet, consuming less than 130 grams of carbohydrates per day, while the other group follows an MD. Both groups receive personalized dietary counseling based on the six steps of the IM framework. The intervention aims to promote weight loss (10–15% of body weight) and enhance diabetes self-management through structured nutrition education, goal setting, behavioral strategies, and regular follow-ups with trained dietitians to achieve remission of diabetes.

Both groups receive comparable frequency and intensity of counseling sessions to ensure standardized behavioral support, differing only in dietary composition. Educational materials and personalized meal plans are provided in accordance with the assigned diet.

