#### Step 6: planning for evaluation

This final step in the IM process focuses on developing a plan to evaluate the effectiveness and implementation of the intervention (54). While this manuscript centers on the design of the first phase of the trial using the IM approach, preliminary evaluation plans have been developed to ensure a comprehensive assessment in subsequent stages. The trial outcomes will be evaluated to determine the intervention’s effectiveness in achieving diabetes remission across two diets, and to assess the impact of both the MD and LC diets on weight loss, glycemic control, and diabetes-related metabolic complications. Additionally, the evaluation will assess the feasibility and fidelity of the implementation. It will examine multiple dimensions, including the quality of communication between patients and dietitians, adherence to behavioral changes, and assigned dietary interventions.

On the other hand, the maintenance phase (Phase 2) will include an evaluation of the mobile application’s role in supporting adherence and facilitating communication. Implementation outcomes will also be assessed, including program fidelity, participant acceptability of the diets, and the appropriateness of the tracking tools and questionnaires. These evaluation components will provide valuable insights into both the intervention’s effectiveness and its feasibility for integration into routine clinical practice. Further details will be presented in subsequent articles concerning the mobile app design and features, as well as the intervention results.

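### The effectiveness of education is to be judged from education exposure or knowledge change, which are not randomised, so the analysis can show only an association and is not intention to treat.

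*Protocol article*

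**What the plan says.** **Education analysis (Statistical methods).** "The effectiveness of the educational component will be evaluated by examining the association between education exposure or knowledge change" and the primary and secondary outcomes. The tool is "multivariable regression models adjusted for relevant baseline covariates". The same section opens with "All analyses will be conducted according to the intention-to-treat principle" and sets significance at p < 0.05. The Outcomes section labels the secondary outcomes exploratory. No such label is attached to the education analysis, which also takes in the primary outcome.

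**What is randomised (Intervention).** "Participants are randomly allocated to one of two dietary intervention arms: a low-calorie MD or a low-calorie LC diet".

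**What both arms receive (Phase 1).** "Both groups receive personalized dietary counseling based on the six steps of the IM framework". "Both groups receive comparable frequency and intensity of counseling sessions to ensure standardized behavioral support, differing only in dietary composition". The content follows the diet: "Educational materials and personalized meal plans are provided in accordance with the assigned diet".

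**Programme-level statements.** Step 6 plans to use trial outcomes to determine the intervention's "effectiveness in achieving diabetes remission across two diets". The Conclusion says that effectiveness will be evaluated once the intervention has been implemented. The end of the Introduction gives the trial's aim as a comparison of the two diets.

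**The concern.** The plan attaches a causal word, effectiveness, to a regression on something that participants partly choose. By design the arms do not differ in how much education they get, so the randomisation provides no education contrast. What remains is variation between individuals in sessions attended or knowledge gained, and two routes can link it to remission without any effect of education.

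- **Confounding by motivation and adherence.** A motivated participant attends, learns, follows the diet and loses weight. The Strengths and limitations section itself expects low education and low socioeconomic status to hinder both dietary adherence and attendance at counselling.
- **Reverse causation.** Table 3 in Step 3 uses body-composition results at visits and three-monthly blood tests as reinforcement. A participant who is improving therefore gets encouraging feedback and may engage and learn more because of it.

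The authors hope that centres will institutionalise the programme (Step 5) and will explore adapting it to other low-resource settings (Conclusion). An association reported as effectiveness would be used as evidence for those decisions.

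**Working it through.** **1. The plan's own figure.** The sample size concerns the diet contrast only. Inputs from Sample size calculation: 57% versus 15%, two-sided alpha 0.05, power 80%; 1:1 allocation is assumed.

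- Arcsine formula: n per arm = 2 × [(1.96 + 0.84) / h]², with h = 2·arcsin√0.57 − 2·arcsin√0.15 ≈ 0.916. This gives 18.7, rounded up to 19 per arm, or 38 in total, as stated.
- With 20% attrition, 50 × 0.80 = 40 evaluable.

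The figure reproduces. Nothing in it concerns education.

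**2. The statements side by side.**

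| Question | What the protocol gives |
|---|---|
| Is education randomised? | No. Diet is the only randomised factor (Intervention). |
| Do the arms differ in amount of education? | Not by design. Content follows the diet (Phase 1). |
| When does the explanatory variable arise? | After randomisation (exposure received, knowledge change). |
| What is adjusted for? | Baseline covariates (Statistical methods). |
| Which principle governs? | Intention to treat, for all analyses (Statistical methods). |

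Two things follow. Baseline covariates cannot account for motivation, adherence or clinical response that develops during follow-up. And an analysis that orders participants by education received or knowledge gained is not by randomised assignment, so the intention-to-treat statement cannot cover it.

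**3. How large the bias could be.** The documents give no figure, so this is an illustration. Assumptions not in the documents: education has no effect; an unmeasured standardised trait U has correlation r with exposure (or knowledge change) E and log-odds effect b per SD on remission.

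- E = r·U + √(1 − r²)·noise
- logit P(remission) = logit(0.57) or logit(0.15) by arm, plus b·U
- Fitted model: remission on arm and E; 2,000 runs per setting, of which at least 1,982 gave a usable fit.

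Share of runs with p < 0.05 for E, and median odds ratio (OR) per SD of E:

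| N | r | b = 0.5 | b = 1.0 |
|---|---|---|---|
| 40 | 0 | 3.6%, OR 1.03 | 3.0%, OR 0.99 |
| 40 | 0.3 | 5.5%, OR 1.18 | 8.0%, OR 1.31 |
| 40 | 0.5 | 6.8%, OR 1.29 | 18.6%, OR 1.62 |
| 40 | 0.7 | 11.9%, OR 1.43 | 34.2%, OR 2.00 |
| 50 | 0 | 4.1%, OR 1.00 | 3.9%, OR 1.00 |
| 50 | 0.3 | 6.2%, OR 1.15 | 11.7%, OR 1.32 |
| 50 | 0.5 | 9.3%, OR 1.30 | 22.6%, OR 1.58 |
| 50 | 0.7 | 15.8%, OR 1.42 | 43.2%, OR 1.98 |

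With r = 0 the median OR is about 1 and the test is slightly conservative. With r above 0 the OR moves away from 1 although education does nothing, and adjusting for arm does not prevent it. Going from 40 to 50 participants leaves the OR much the same and raises the rejection rate, as expected for bias rather than noise. U here stands for whatever the baseline covariates fail to capture.

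**4. Programme-level statements.** Both arms receive the Intervention Mapping programme and no arm goes without it. The randomised comparison therefore identifies the difference between the diets. Change within an arm has no control and may also reflect regression to the mean, medication and other concurrent influences.

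**The case against.** The best defence is that the sentence itself describes an association, that the definition of exposure and the covariate list may stand in a fuller document, and that Step 6 is called preliminary and can be read as comparing the two diets. The second part stands: missing definitions are no fault here. The Step 6 reading is also fair, so that passage needs only a clarification. The first part does not rescue the sentence, because the association is offered as the means of evaluating effectiveness and nothing in the article withdraws that word.

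Three stronger readings are tempting, and the documents do not support them.

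- **That the whole programme will be judged from post-randomisation exposure.** Only the educational component is treated this way. Step 6 refers to trial outcomes across the diets. The limit on programme-level claims is a separate one: there is no comparator without the programme.
- **That a positive result is bound to appear.** The simulation shows a raised false-positive risk, from barely above nominal to 43% in the worst setting tried, and not near-certainty.
- **That dropouts alone would create the association, having little exposure and counting as non-remitters.** The protocol does not say that dropouts count as failures; it leaves missing data to appropriate methods. A dropout without a follow-up knowledge score would also have no knowledge change to analyse. Participants who respond poorly but stay keep the same monthly visits.

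It is also too strong to say that both arms get identical education. The amount is meant to be comparable, while the materials follow the diet.

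**Conclusion.** The concern holds for the education analysis. As written, it labels a confounded post-randomisation association as effectiveness, and it contradicts the intention-to-treat statement in the same section. This conclusion follows from the text and needs no numerical assumption.

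The size is uncertain. Under the assumed confounding, with 40 evaluable participants and no true effect, the nominal 5% test rejects in about 6% to 8% of runs at r = 0.3, 7% to 19% at r = 0.5 and 12% to 34% at r = 0.7. The median spurious odds ratios per SD are about 1.2 to 1.3, 1.3 to 1.6 and 1.4 to 2.0. The values of r and b are assumptions.

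The programme-level statements in Step 6 and the Conclusion need a narrower wording for a different reason, the absence of a group without the programme. The randomised diet comparison, the primary endpoint and the sample size are not affected.

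**What to change.** **Statistical methods.**
- Replace the promise to evaluate the effectiveness of education with an exploratory analysis of how education exposure and knowledge change are associated with outcomes, and state that no causal claim will be made.
- Exempt this analysis from the intention-to-treat statement.
- Include randomised arm in the model.
- Use exposure or knowledge change measured before the outcome it is related to.
- If knowledge is measured part-way through Phase 1 (the article gives no schedule for repeating that questionnaire), a landmark form can be used: exposure up to that point related to the month-6 outcome among those still followed. This reduces survival bias and reverse causation. It does not remove confounding by motivation, so the change of wording is needed either way.
- Keep the model small. At the planning rates, (57% + 15%) / 2 = 36% of 40 evaluable participants is about 14 remissions, so four terms would have 14.4 / 4 = 3.6 events each.

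**Step 6 and Conclusion.** Limit effectiveness claims to the randomised contrast between the Mediterranean and low-carbohydrate diets, and describe change within each arm as uncontrolled.

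**Cost.** A few sentences and a small change to an exploratory model, with no new visits, measurements or participants. The price is a more modest claim about education and the programme.
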